#### Identification of predictive markers and affected histological and cellular processes

2.4.3

Our overarching objective involves the discernment of tumor characteristics and the elucidation of a mechanistic basis underpinning responses to or resistance against the therapeutic intervention. Therefore, secondary outcomes of the HISTOTHERM study are the characterization of histologic and cellular differences within subgroups of patients to determine markers and key regulated processes involved in or activated by the combination therapy. To achieve these goals, comprehensive immunohistological and proteomic analyses on tissue and blood-based analyses will be undertaken.

Residual diagnostic tissue samples collected pre-treatment, during treatment (dose of 12 Gy) and at follow-up are used for analyses. Where available, tissue from the primary diagnosis is included in the analysis. Biopsies are routinely paraffin-fixed and embedded, followed by cutting of all required sections. After completion of routine diagnostics, study-specific immunohistochemical staining will be carried out on Formalin-fixed Paraffin Embedded (FFPE) tissue by trained staff of the CCCF biobank to obtain a comprehensive picture of the core processes involved.

Among the principal foci of investigation are the regulatory dynamics of the immune system, the mechanisms underpinning apoptosis and senescence. Approximately 20 different antibodies will be deployed for immunostaining of key proteins involved in those processes. Immunostaining will be performed in a standardized manner on multiple samples in parallel and will always include positive and negative controls to identify confounding staining effects. Subsequently, sections will be digitized and electronically archived on internal servers for further analysis.

Histologic sections are analyzed by trained staff who are blinded to clinical outcome. Depending on the marker protein under investigation, we will quantify and evaluate staining pattern, tissue distribution, intensity and number of positive and negative cells. Image analysis is supported by digital analysis tools, such as QuPath, which was developed specifically for pathological analysis (38). The tissue separation and cell detection tools are used for image classification and quantification of staining intensity, percentage of positive and negative cells and antibody distribution. Positively stained tissue structures are counted manually.

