We will conduct a two-fold analysis of protein expression patterns, firstly focusing on alterations during the course of the treatment, and secondly comparing expression between patient groups displaying varying treatment responses. Histologic and clinical regression will be statistically correlated with the histopathologic findings. In pursuit of predictive histologic markers for therapy response, we will perform rate modeling using Poisson regression with offset and exploratory factor analysis. Cluster analysis will be employed to identify relevant biological processes in the tissue. The identified proteins and processes will lay the foundation for further investigations for therapy prediction.

Further, mass spectrometry-based proteomics is used to identify proteome alteration from the limited biopsy material. Proteome profiling by liquid chromatography – tandem mass spectrometry is performed essentially as described in our recent benchmarking study (39). From the biopsies before and if applicable during treatment and from the primary diagnosis, 1-2 sections of 10 μm section thickness will be prepared for proteomic analysis after micro- or macrodissection and measured on a Q-Exactive+ high performance mass spectrometer. Due to the scarcity of sample material, we focus on abundance proteomics. Data-independent acquisition with label-free quantification will be used.

We expect a proteome coverage in excess of 3000 proteins measured in our micro- or macrodissected tissue slides. For analyses, we will consider proteogenomic probing of common genomic alterations. Statistical evaluation will involve supervised and unsupervised approaches. Hierarchical clustering will be employed to identify proteomic subgroups, and algorithms that are tolerant for a low frequency of missing values will be considered. Protein expression will be associated with outcome data using multivariate Cox-type analyses, including consideration of boosting steps if required. We will also consider multivariate linear models, as highlighted by linear models of microarray analysis, including consideration of variable selection by tools such as elastic nets. Multiple testing correction will be considered. The proteomic profiles will be correlated with treatment stage and success to identify potential protein markers indicating a particularly good or poor response.

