### Sample size calculation

2.5

Due to the exploratory nature of the study and for pragmatic reasons (63), 40 patients will be prospectively enrolled in the study. From each included patient, three biopsies will be taken and tissue from primary diagnosis or recurrence will be analyzed. Specimen staining is envisioned using approx. 20 antibodies. This results in 80 histological sections per patient to be processed and evaluated, and a total number of up to 3200 specimens to be examined. For proteome profiling our benchmarking study has highlighted that proteome alterations (e.g. between "responders" and "nonresponders”) are detectable with this sample size even in the presence of inter-individual proteome heterogeneity (39).

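### The marker search names Poisson regression with offset and does not provide for variation between patients; on stained-cell counts its error rate would be well above nominal

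*Protocol article*

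**What the plan says.** Section 2.4.3 of the protocol article describes the tissue work. Depending on the marker, "we will quantify and evaluate staining pattern, tissue distribution, intensity and number of positive and negative cells". Separately, "Positively stained tissue structures are counted manually". Expression is to be examined first over the course of treatment, and "secondly comparing expression between patient groups displaying varying treatment responses".

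For the search itself the article states: "In pursuit of predictive histologic markers for therapy response, we will perform rate modeling using Poisson regression with offset and exploratory factor analysis". The sentence names no outcome, offset or unit of analysis. The section mentions no dispersion parameter, robust variance or patient effect for this model.

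Section 2.5 gives the scale: "40 patients will be prospectively enrolled in the study", and from each of them "three biopsies will be taken and tissue from primary diagnosis or recurrence will be analyzed". About 20 antibodies are planned.

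Section 2.4.2 groups patients by clinical and histologic response in order to compare molecular profiles and survival, and names a generalized linear mixed model with Poisson distribution for evaluation. It does not specify the random effects or say whether that model also governs the marker search.

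**The concern.** A Poisson model with an offset fixes the variance of each count at its mean. If the count is positive cells and the offset is total cells or area, the model treats every cell as an independent observation. The comparison, however, is between groups of patients, so the independent unit is the patient. Patients differ in their true positive fraction for reasons unrelated to response, and this adds variance proportional to the square of the mean. Plain Poisson has no term for it. The standard error then shrinks with every additional cell counted, although the number of patients stays at 40. Entering several biopsies from one patient as separate rows makes this worse.

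At stake is the marker shortlist, which section 2.4.3 describes as the basis for later work on predicting therapy response. Standard errors that are too small would put unrelated markers on that list and favour abundant markers, where the understatement is largest. Multiplicity correction, which the article says only will be considered, and only in the proteomics text, would not repair wrong standard errors.

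**Working it through.** **The plan's own figure.** (3 biopsies + 1 primary or recurrence sample) × 20 antibodies = 80 sections per patient, and 80 × 40 patients = 3200. This matches section 2.5. The article gives no alpha, power or error rate for the marker search, so there is no stated operating characteristic to reproduce.

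**Inputs from the article:** 40 patients, about 20 antibodies, up to four tissues per patient, and a comparison between response groups.

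**Assumptions, not in the article:** positive-cell count as outcome with total cells as offset; a two-sided 0.05 test; the mean positive count per patient (μ); the between-patient coefficient of variation of the true rate (CV); and the split into response groups.

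**Formula.** With no true association, the variance of a patient's count is μ + μ²CV², against μ under Poisson. The inflation is therefore φ = 1 + μ·CV², and the actual error of a nominal 5% test is 2·[1 − Φ(1.96/√φ)].

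- μ = 5, CV 0.3: φ = 1 + 5 × 0.09 = 1.45, so the standard error is too small by a factor of √1.45 = 1.2 and the error is about 10%.
- μ = 40, CV 0.5: φ = 1 + 40 × 0.25 = 11, factor 3.3, error about 55%.
- μ = 200, CV 1.0: φ = 1 + 200 × 1 = 201, factor 14.2, error about 89%.

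**Simulation check.** 4,000 runs per setting, 40 patients split 20/20, gamma variation between patients, and total cells varying between patients. Each cell of the table shows closed form / simulation.

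| Mean positive count | CV 0.3 | CV 0.5 | CV 1.0 |
|---|---|---|---|
| 5 | 10% / 11% | 19% / 20% | 42% / 45% |
| 20 | 24% / 25% | 42% / 45% | 67% / 68% |
| 40 | 36% / 38% | 55% / 58% | 76% / 77% |
| 200 | 65% / 68% | 78% / 80% | 89% / 89% |

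A 28/12 split gives nearly the same values. With CV 0 the simulated error is 4.0-5.4%, so the inflation comes from the between-patient variation alone. At a mean of 200, even CV 0.1 gives 28%.

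**When would most unrelated markers test positive?** An error above 50% needs φ > (1.96/0.6745)² = 8.44, that is CV > √(7.44/μ): 0.09 at a mean of 1000, 0.19 at 200, 0.39 at 50, 0.61 at 20, 0.86 at 10 and 1.22 at 5.

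**Expected false markers if all 20 are unrelated, at CV 0.5:** 20 × 0.804 ≈ 16 (mean 200), 20 × 0.578 ≈ 12 (mean 40), 20 × 0.449 ≈ 9 (mean 20) and 20 × 0.198 ≈ 4 (mean 5). A valid 5% test gives 20 × 0.05 = 1.

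**Several biopsies.** With three biopsies per patient entered as independent rows (300 runs, mean about 200 per biopsy), the plain Poisson error is 80% at patient CV 0.3, and 90% at patient CV 0.5 with biopsy CV 0.3.

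**Alternatives on the same simulated data.** With one value per patient, quasi-Poisson holds about 5-7% and a Welch t-test on patient log-rates 4.0-5.8%. With three biopsies, regression on patient means gives 4-7%, and generalized estimating equations with robust standard errors give 6-10%, slightly liberal with 40 clusters.

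**The case against.** Much of the case on the other side stands.

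- **Outcome and offset are not stated.** Section 2.4.3 also lists staining pattern, tissue distribution, intensity and percentages. Counts with a cell or area offset are the natural reading of a rate model, but an inferred one. A reader might go further and infer that the marker is wrongly placed as the outcome where prediction needs response as the outcome. The sentence does not say on which side of the model the marker stands, so that is not a demonstrated error.
- **A mixed model appears elsewhere.** A reader might infer that the plan ignores variation between patients altogether. Section 2.4.2 does not allow that: it names a Poisson mixed model for an overlapping comparison. That section does not, however, define random effects or refer to the marker search, and a patient intercept alone would miss variation between biopsies of one patient.
- **The article is condensed.** Dispersion terms and variance estimators are often left to a fuller plan. This explains missing detail. It does not change the fact that the model family named here, run as named, gives wrong standard errors on such counts.
- **Most markers, or only some?** A reader might infer that nearly all of the 20 markers would be declared associated. The article gives neither counts nor CV, and for sparse markers or manually counted structures the error can be as low as 11%, about 2 of 20.
- **The analysis is exploratory.** No significance rule is stated and the primary outcome does not depend on this model. The harm is a misleading shortlist, not a failed confirmatory test.

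**Conclusion.** The point holds in conditional form, at moderate severity. The marker search names Poisson regression with offset and makes no provision there for extra-Poisson variation or repeated samples, and the mixed model in section 2.4.2 is neither specified nor linked to it. If the model is applied as written to stained-cell counts, its standard errors reflect cells rather than the 40 patients.

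For a nominal two-sided 5% test and a CV of 0.3 to 1.0, the simulated error is 11-45% at a mean count of about 5, 38-77% at about 40 and 68-89% at about 200. The direction does not depend on the exact inputs: any between-patient variation raises the error above nominal. The size depends on counts, CV and alpha, none of which the article gives. Many unrelated markers could therefore look associated with response, and for abundant markers most could.

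**What to change.** In section 2.4.3, or in the analysis plan it rests on:

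1. Define the outcome, the offset and the unit of analysis, with the patient as the unit.
2. For comparing expression between response groups, replace plain Poisson with quasi-Poisson or negative-binomial regression with the offset, on one pre-treatment value per patient.
3. Where several time points are analysed, use a mixed model with patient and sample-level effects. State whether this is the mixed model of section 2.4.2, and specify its random effects there.
4. For prediction, regress response on the pre-treatment positive fraction, for example with Firth logistic or proportional-odds regression, one value per patient.

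This changes wording and analysis code only; the data stay the same. The price is wider intervals and fewer nominally significant markers. With 40 patients, quasi-Poisson remains very slightly liberal (about 5-7% in the simulations), which is acceptable for an exploratory shortlist.

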Predictive histologic and/or molecular markers, as used in systemic treatment (28), have not yet been identified for hyperthermia. The clinical potential of predictive markers for hyperthermia lies in patient-tailored therapy, which may include decision support for treatment escalation or de-escalation. Furthermore, the identification of predictive markers offers the opportunity to infer previously unknown mechanistic processes that are affected by the combination therapy. In particular, immunological processes are considered to be relevant (29).

In the HISTOTHERM study, clinical and histological tumor control rates in patients with locally advanced recurrent breast cancer will be analyzed over time, as well as the tolerability of the therapy and the quality of life of the patients during the treatment. In addition, our study intends to identify potential markers and processes which play a role in the combination treatment. These may help to define markers that could guide treatment decisions in the future. Finally, the study will allow the longitudinal observation of histological and cellular changes.

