Immunophenotyping of lymphocyte subpopulations in the peripheral blood will be performed to measure immunomodulatory activities of radiotherapy in combination with hyperthermia on the innate and adaptive immune system. It is well known that Hsp70 as one of the danger associated molecular patterns (DAMPs) can stimulate NK cell mediated immune responses (58). In a pilot study and in phase I and II clinical trials beneficial effects could be demonstrated by *ex vivo* Hsp70/IL-2 stimulated NK cells in patients with advanced colon and lung cancer (59–61). In this study we aim to measure the proportions of major lymphocyte subpopulations such as CD3+/CD4+ CD3+/CD8+ T helper and cytotoxic T lymphocytes, CD3+/CD94+ NK-like T cells, CD3+/CD4+/CD25+/FoxP3+ immunosuppressive T regulatory cells, CD19+ B cells, and CD3-/CD56+, CD94+, NKG2D+, NKp30+, NKp40+, CD69+ NK cell subpopulations in the course of therapy by multiparameter flow cytometry using fluorescence-labeled antibodies (59, 62). The aim is to identify an immune cell signature which might be able to predict clinical outcome.

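### The marker analyses aim at prediction, but none of the stated steps assesses it in patients not used for selection; at 40 patients, same-patient performance would be strongly optimistic

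*Protocol article*

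**What the plan says.** The predictive aim appears for each data source in section 2.4.3 of the protocol article.

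- **Histology:** "In pursuit of predictive histologic markers for therapy response, we will perform rate modeling using Poisson regression with offset and exploratory factor analysis". The marker set is stated: "Approximately 20 different antibodies will be deployed for immunostaining of key proteins involved in those processes".
- **Proteome:** "We expect a proteome coverage in excess of 3000 proteins measured in our micro- or macrodissected tissue slides". Protein levels are to be related to outcome by Cox-type models, with boosting if needed, and by linear models, "including consideration of variable selection by tools such as elastic nets". Multiplicity correction is something to be considered; no method is named.
- **Blood:** exosomal Hsp70 and circulating tumour cell counts are discussed as possible predictors. For the lymphocyte subsets, "The aim is to identify an immune cell signature which might be able to predict clinical outcome". No model is named for that signature.

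Section 2.5 sets the size without a power or precision argument: "Due to the exploratory nature of the study and for pragmatic reasons (63), 40 patients will be prospectively enrolled in the study". It adds that proteome differences between responders and non-responders are detectable at this size. The Introduction describes the clinical potential of predictive markers for hyperthermia in general as patient-tailored therapy, "which may include decision support for treatment escalation or de-escalation".

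The article mentions no hold-out set, cross-validation, bootstrap correction or external cohort, and no measure of discrimination or calibration.

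**The concern.** Detecting a difference and predicting an outcome are different tasks, and the stated tools are tied to the second while mostly delivering the first.

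The histology model shows this most clearly. A Poisson rate model with an offset is most naturally read as having stained-cell counts as the outcome. It then tests whether the mean rate differs between response groups. It does not say how well the marker separates responders from non-responders.

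The proteome raises a second problem. When a few variables are chosen from thousands in 40 patients, the fit in those same patients is inflated by the choice. Multiplicity correction, even if applied, controls errors of single tests. It does not remove the optimism of a selected multi-variable signature.

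At stake is what the study hands on. A signature that looks excellent in the patients who produced it, with no corrected figure beside it, is a poor basis for choosing what to take into later work.

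**Working it through.** **The plan's own figure.** Section 2.5 derives only a workload: (3 biopsies + 1 primary or recurrence tissue) x 20 antibodies = 80 sections per patient, and 80 x 40 = 3200 specimens. Both figures reproduce. Neither bears on prediction, and the 40 has no formula behind it to check.

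**Inputs.** From the documents: 40 patients (2.5), more than 3000 proteins (taken as 3000) and about 20 antibodies (2.4.3). By count: 11 lymphocyte subsets, from a list in 2.4.3 that is introduced as examples. Assumed, because the documents do not give it: 12, 20 or 28 responders of 40. Also assumed: independent normal features, complete data and no true signal.

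**Method.** 200 simulated datasets per proteome setting and 300 per small-panel setting. The best k features by t statistic form a t-weighted score; where all features are used, a linear discriminant is fitted. The AUC is taken in the same patients, by 5-fold cross-validation with selection repeated inside each fold, and in new patients. The small panels were run at 20 and 12 responders; 28 mirrors 12, since it only swaps the group labels.

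| Noise features | Signature | Mean same-patient AUC | Share of runs with AUC exactly 1 |
|---|---|---|---|
| 3000 proteins | best 5 | 0.97-0.98 | 3-14% |
| 3000 proteins | best 10 | 0.99-1.00 | 30-58% |
| 3000 proteins | best 20 | 1.00 | 91-98% |
| 20 antibodies | best 5 | 0.80-0.82 | 0% |
| 11 blood subsets, one time point | best 3 | 0.74-0.76 | 0% |
| 11 blood subsets, one time point | all 11 | 0.80-0.83 | 0% |
| 22 (two time points) | all, unpenalised | 0.94-0.95 | 4% |
| 33 (three time points) | all, unpenalised | about 1.00 | 73-86% |

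In new patients the mean AUC was 0.50 in every row.

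**Does resampling cure it?** With selection repeated inside each fold, the mean AUC was 0.49 to 0.51 throughout. If proteins are first chosen on all 40 patients and only the weights are cross-validated, it stays at 0.96 to 1.00. The place of the selection step therefore decides the result.

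**Single tests.** At the 5% level, 3000 x 0.05 = 150 noise proteins are expected to pass. With independent tests, the chance of at least one false positive is 1 - 0.95^11 = 43% for 11 subsets and 1 - 0.95^20 = 64% for 20 antibodies.

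**What a just-significant mean difference is worth.** With normal markers of equal variance and an assumed 28:12 split, the standardised difference that just reaches 5% is d = 2.024 x sqrt(1/28 + 1/12) = 0.698. Then AUC = Phi(d/sqrt 2) = 0.69, and the share classified correctly at the midpoint is Phi(d/2) = 64%. With 20:20, d = 2.024 x sqrt(1/20 + 1/20) = 0.640, AUC = 0.67 and 63% are correct. This illustrates a marker exactly at the threshold; it is not a forecast.

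**The case against.** The strongest reply is that this is an article. How an elastic net or boosting model is tuned, resampled and scored commonly sits in a full protocol or analysis plan, and neither is shown. The article offers these tools only as options and nowhere says that uncorrected performance will be reported. That limits the point: a reader might infer that validation has been ruled out, and the text does not support this. What remains is that the article does not leave the marker analysis open. It names tools in detail, ties one of them directly to the predictive aim, and lists no step that would test prediction.

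The second reply is that the study is exploratory. Section 2.5 says so, and 2.4.3 presents the markers as groundwork for later prediction research. This stands and lowers the weight of the point. It does not remove it, because optimism is greatest in small exploratory datasets.

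Three stronger readings are tempting and should be resisted.

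- **The tools only compare means or select variables.** Cox, boosting and elastic-net models do produce predicted values. The gap is that no stated step measures how good those values are outside the selecting patients.
- **Noise will look perfect everywhere.** That fits the proteome. For 11 blood subsets at one time point the figure is 0.74 to 0.83. It nears 1.00 only if all subsets at three time points are fitted without penalty, which the article does not propose.
- **The signature is meant to steer escalation.** The Introduction says this of the potential of such markers in general, and not as the use planned for this study's results.

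The dependent variable of the Poisson model is also not stated; reading it as a cell count is an inference, though the natural one.

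**Conclusion.** The concern holds in limited form. Section 2.4.3 pursues predictive markers and signatures in 40 patients, and none of its stated analyses assesses prediction in patients not used for selection. If same-patient performance were reported, pure noise could show a mean AUC of about 0.97 to 1.00 for a 5- to 20-protein signature and about 0.74 to 0.83 for the one-time-point blood panel, against a true 0.50.

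These sizes rest on independent features, complete data, an assumed 12 to 28 responders of 40, and simple t-based selection standing in for the tools the article names. Correlated proteins reduce the effective number of features and would soften the inflation somewhat. Given the exploratory framing, this is a worthwhile, low-cost improvement to the analysis and to how its results are described.

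**What to change.** For any marker or signature to be described as predictive:

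1. Model response or survival as the outcome with the marker as predictor. Analyse pre-treatment and on-treatment markers separately, since both are planned and they answer different questions.
2. Report the AUC (response) or C-index (survival) with its interval, from nested cross-validation or bootstrap optimism correction. Repeat all selection and tuning inside each resample.
3. Never report the apparent value alone.

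Where this is not done, describe the outputs as candidate markers only.

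A rule that the interval must exclude 0.5 is not advised. In the simulations a single cross-validated AUC at 40 patients had an SD of about 0.10 to 0.16, so such a rule would put a confirmatory hurdle on an exploratory study and could discard useful candidates.

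The cost is some extra computing and a few lines of analysis text, with no further patients or samples. Reported performance will be less favourable and its intervals wide.
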